A potential downside to online CBT is the high dropout rate found in earlier studies.^33 35^ It has been argued that a strong therapeutic alliance might support adherence to online treatment and mediates treatment effects.^36^ Therapeutic alliance is defined as a positive emotional bond between client and therapist, whereby both parties agree on the tasks and goals of the treatment.^37^ The client–therapist relationship might also explain why online treatments are more effective with therapist guidance than without.^31^ Concerns have been raised that developing a therapeutic relationship might be more difficult when non-verbal communication is absent.^38^ However, studies in non-bereaved samples indicate that developing a strong therapeutic alliance is possible during online treatment^33^ and that therapeutic alliance is often related to online treatment outcomes,^39^ but not always.^33^ More research is needed to further examine the interrelations of the quality of client–therapist relationship, drop-out and treatment outcomes in online CBT.

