## Methods and analysis

### Design

A two-arm (online CBT vs waiting list) multicentre open label parallel randomised controlled trial (RCT) will be conducted. Randomisation will take place after the participant is screened for eligibility-based inclusion criteria (described below). A random number generator (www.random.org) will be used by a blinded independent researcher, to perform the blocking randomisation procedure. An allocation ratio of 1:1 will be applied.

Participants allocated to the online CBT condition receive treatment within 1 week after allocation. All participants will be asked to fill in questionnaires (described below) at baseline (T1), 12 weeks postallocation (T2 for the intervention condition and T1a for waitlist controls) and 20 weeks postallocation (T3 for the intervention condition and T1b for waitlist controls). For participants in the waiting list control group, at the end of the 20-week waiting period after which they will receive online CBT, they will be asked to fill in T2 and T3 12 and 20 weeks after starting treatment, respectively (see figure 1). A link to online questionnaires will be sent to the participants by a non-blinded member of the research team at each time point. A waitlist control group (instead of a no treatment control group) is chosen to increase the likelihood of continued study participation by guaranteeing that all participants receive treatment. Furthermore, the inclusion of a waiting list control group allows a treatment versus no treatment comparison that will provide knowledge about the effects of treatment relative to natural recovery from loss.

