### Sample size

To test our primary hypothesis (hypothesis 1), a test for each outcome separately (PCBD, PTSD and depression) will be conducted to assess the effects of online CBT versus waitlist controls. To find a difference between two groups (online CBT vs waitlist controls) of at least a medium effect size (f=0.25; based on prior research^22 28 40^) with a power of 80%, an α of 0.017 (corrected for multiple testing, that is, 0.05/3, as there are three primary outcome measures (PCBD, PTSD and depression), and a strong association (r=0.50) between the preassessment and postassessment, a sample size of 23 per condition is sufficient. Taking into account an average dropout rate of 19%,^22^ a total sample size of 55 (46+9) is required to test hypothesis 1.

Because our data are nested (repeated measures) (level 1) within individuals (level 2), and possibly within families sharing the same household (level 3), multi-evel modelling will be performed to test hypothesis 1. Conducting a power analysis within a multilevel framework is not feasible for various reasons.^42^ Our power analysis is therefore based on a repeated measures analysis of variance.

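### The 19% drop-out allowance is taken on the 46 needed instead of on those randomised, so the stated total of 55 should be 57 (58 for equal arms): a minor arithmetic error

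*Protocol article*

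**What the plan says.** The Sample size section of the protocol article sizes the trial for hypothesis 1 with these inputs:

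- effect: "of at least a medium effect size (f=0.25; based on prior research";
- significance level: "an α of 0.017 (corrected for multiple testing, that is, 0.05/3", for three primary outcomes;
- power: 80%;
- correlation: "a strong association (r=0.50) between the preassessment and postassessment".

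This gives 23 per condition, 46 in all. The section then brings in an average drop-out rate of 19%, taken from a cited source, and states that "a total sample size of 55 (46+9) is required to test hypothesis 1". It explains that a power analysis in a multilevel framework was not feasible: "Our power analysis is therefore based on a repeated measures analysis of variance". The Design section adds: "An allocation ratio of 1:1 will be applied". The Statistical analyses section plans multilevel models that include everyone who enters the study.

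**The concern.** The bracketed sum shows how the allowance was made: a share of the number needed at the end was added to that number. A drop-out rate is a share of those who start. The three figures 19%, 46 and 55 therefore cannot all hold. If 19% of 55 are lost, fewer than 46 remain. If 46 are to remain out of 55, drop-out must stay below 19%.

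At stake is the headline recruitment target, which the article calls required. A reader would take it that 55 randomised secure the 46 on which the power statement rests, and at the plan's own rate they do not.

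**Working it through.** **Inputs.** From the Sample size section: f = 0.25, r = 0.50, α = 0.017, power 80%, 46 needed, drop-out 19%, total 55. Two groups and two occasions are inferred from the section's reference to a pre- and a post-assessment. The exact match in step 1 supports that reading.

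**Step 1: reproduce the base of 46.** For the group-by-time interaction with m = 2 occasions, the noncentrality is λ = f² × N × m/(1 − r), with 1 and N − 2 degrees of freedom.

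- N = 46: λ = 0.0625 × 46 × 2/0.5 = 11.5; power 81.4%.
- N = 44: λ = 0.0625 × 44 × 2/0.5 = 11.0; power 79.3%.

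The smallest even total that reaches 80% is 46, so 23 per condition is reproduced exactly. A purely between-group test on the same inputs would need 128 and does not fit the stated figure.

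**Step 2: reproduce the 55.** 46 × 0.19 = 8.74, rounded up to 9; 46 + 9 = 55. This is the printed sum.

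**Step 3: what 55 covers.**

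- Drop-out covered: 9/55 = 16.4%, not 19%.
- Expected with complete data at 19%: 55 × 0.81 = 44.55, about 1.4 short of 46.

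**Step 4: the consistent total.**

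- Overall: 46/0.81 = 56.8, so 57; check: 57 × 0.81 = 46.2.
- Per arm: 23/0.81 = 28.4, so 29 per arm and 58 in all; check: 58 × 0.81 = 47.0.

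**Step 5: the cost in power, same model, α = 0.017.**

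| Participants with complete data | Power |
|---|---|
| 44 | 79.3% |
| 44.55 (expected from 55) | 79.9% |
| 45 | 80.4% |
| 46 | 81.4% |

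The expected loss is 81.4 − 79.9 = 1.5 percentage points. With α taken as exactly 0.05/3, power at 44.55 is 79.7% and at 46 it is 81.2%.

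**The case against.** The strongest reply is that nothing of substance is lost, and much of it stands. The criterion is 80% power, and 46 overshoots it because the arms were kept equal. On the same model 45 participants already reach 80.4%, and 45/0.81 = 55.6, so 56 randomised would do. Against the power target, 55 is one person short and expected power is 0.1 of a point low.

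The count of 44.55 also treats a drop-out as contributing nothing. The planned multilevel model keeps everyone who enters, so someone who supplies only some of the assessments still adds information, and someone who stops treatment may still return questionnaires. The loss is probably smaller than step 5 shows. None of this makes the sum right: the plan chose to size the trial on a repeated-measures ANOVA and to inflate for drop-out, and that inflation does not match its own rate.

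Two stronger readings are tempting, and the documents support neither.

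- **The odd total.** A reader might infer that 55 conflicts with the allocation ratio. It does not: a 1:1 ratio can end at 27 and 28, and the corrected 57 is odd too. The figure of 58 is needed only if the arms are to be equal.
- **The rate itself.** The introduction says "A potential downside to online CBT is the high dropout rate found in earlier studies", and a reader might conclude that 19% is too low or leaves no margin. That passage gives no figure to set against 19%, and the source of the 19% is not at hand. The point here concerns how the rate is applied, not its value.

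**Conclusion.** The point holds as a minor arithmetic error. The total is wrong as written: on the plan's own 46 and 19% it should be 57, or 58 for equal arms, so the shortfall is two or three participants. Expected power falls by about 1.5 points, from 81.4% to 79.9%.

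A reader might infer that the trial is underpowered. The figures do not support that: power stays at about 80%, and the intention-to-treat multilevel analysis works in the trial's favour. No test and no planned comparison changes.

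The correction of the total rests only on the printed 46 and 19%. The power figures rest in addition on the two-occasion interaction form of the ANOVA, which is inferred from the wording and from the exact match with 23 per condition, and on counting only participants with complete data.

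**What to change.** Change the last sentence of the first paragraph under Sample size in one of two ways.

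- **Keep 46 as the number needed.** State the total as 46/(1 − 0.19) = 57, or 58 (29 per arm) if equal arms are wanted. This costs two or three more participants. The article says that recruitment had not begun at submission, so at that stage the target could be changed without affecting conduct.
- **Keep 55.** State that at 19% drop-out about 44 to 45 participants with complete data are expected, with about 80% power (79.3% at 44, 80.4% at 45) on the repeated-measures ANOVA at α = 0.017, and that the multilevel analysis will also use partial data. This costs no participants.

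Either way, say that the 19% applies to those randomised.

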### Intervention

Online CBT will consist of eight one-on-one sessions, called lessons, offered within a timeframe of 12 weeks. Eight sessions have shown to be sufficient to yield clinically relevant effects in prior research.^40^ Following Dutch guidelines for grief-specific CBT,^42^ central components of the treatment are exposure, cognitive restructuring and behavioural activation. In the first session, psychoeducation is offered, including information about possible emotional reactions to the death of a loved one in a traffic accident and processes that might foster or hamper recovery. A rationale for the CBT interventions is provided.

Then, sessions 2–4 are focused on exposure; the circumstances and story of the loss are presented in detail, and the participant is encouraged to confront stimuli that s/he tends to avoid. Exposure is conducted by imaginary exposure assignments and by writing assignment that have proven to be effective in prior research.^30^ These writing assignments are focused on writing a detailed narrative of the loss and its circumstances.

The next sessions (5 and 6) focus on identifying and changing negative cognitions that hamper adjustment (ie, cognitive restructuring); specific attention is paid to cognitions connected with responsibility/guilt and anger that may be experienced following the accidental death.^10^ Cognitive restructuring assignments are provided to gain an alternative perspective on negative thoughts about the self, life, the future, through (1) psychoeducation about common unhelpful thoughts, (2) identifying one’s own unhelpful thoughts and (3) challenging these thoughts. Participants are instructed to undertake these three steps by providing a daily description of (1) an emotional moment/event, (2) their thoughts during this event, (3) their feelings (and intensity of these feelings on a scale of 1–10), (4) their behaviour, (5) evaluation of their thoughts) and (6) alternative helpful thoughts.

In sessions 7 and 8, participants are encouraged to re-engage in previously valued social, recreational and occupational activities in order to facilitate the process of adjustment. Behavioural activation assignments are focused on writing about valued activities and making plans to achieve valued goals. Session 8 is also focused on what the participant has learnt and how to deal with difficulties in the future.

All information and assignments are presented in an online framework, offered via a secure website. Participants receive online written information that consists of psychoeducation, information about treatment content and structure, and homework assignments. As part of the online treatment, participants also listen to a video therapist verbally sharing parts of information that are also presented in text. The video therapists are two members from the traumatic loss network; one male and one female psychotherapist who are middle aged and specialised in treating bereaved people. At the start of the treatment the video therapists introduce themselves and the participant is asked to select one of the video-therapists. The information shared by these video therapists are recorded in video messages in which they read parts of the texts out loud. Each participant, therefore, receives the same information from a video therapist. Direct contact with the video therapist is not possible.

Participants receive weekly asynchronous written feedback from one online therapist on each assignment that they complete online. As mentioned earlier, six online therapists are trained to guide the participants. The online therapists are instructed to contact the participant twice a week; once to encourage participants to log in and complete assignments and once to provide feedback on assignments. In total, they spend 30 min per week on reading assignments and providing feedback. Moreover, participants are encouraged to ask a family member or friend to support them during treatment. This support figure is then informed about the treatment through written information in an online framework.

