### Participants

This RCT is part of a larger ongoing research project (the ‘TrafVic-project’) examining the psychological impact of, and care after, the death of a loved one due to a traffic accident. We expect to recruit the majority of the participants via a survey that started in December 2018 and included the following question: ‘In this study we would like to offer psychological help to persons who experience emotional problems. May we approach you with more information about this offer, if your answers to this questionnaire show that you experience emotional problems?’ Those who answered ‘yes’ will be sent a letter with information about the intervention, the treatment study and an informed consent form (see online supplementary file). A Dutch website (www.rouwnaverkeersongeval.nl) has been developed so that potential participants can read information about the research and treatment. People who are interested can also sign up for the study via this website. Recruitment for this RCT had not started at the time of submission of this manuscript.

10.1136/bmjopen-2019-035050.supp1Supplementary data

To be eligible for study participation, the person must (1) be a family member, spouse or friend of a person who died due to a traffic accident at least 1 year earlier, (2) be ≥18 years of age and (3) meet DSM-5 criteria for PCBD and/or PTSD and/or experience clinically relevant depression, based on questionnaire scores (see below for more details). People are excluded when they do not master the Dutch language or have no internet access.

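### Minor, cheap improvement: a waitlist control could act as support figure to a treated relative or friend and so be informed about the treatment before the 12- and 20-week assessments

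*Protocol article*

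**What the plan says.** In the Intervention section of the protocol article, "participants are encouraged to ask a family member or friend to support them during treatment". The next sentence adds: "This support figure is then informed about the treatment through written information in an online framework". This is encouragement, not a requirement, and what passes to the support figure is written information about the treatment.

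Under Participants, an eligible person must "be a family member, spouse or friend of a person who died due to a traffic accident at least 1 year earlier". The only exclusions listed there concern command of Dutch and internet access.

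Under Sample size and Statistical analyses, the article allows for several participants from one household by adding household as a possible third level of the model.

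Under Design, allocation is 1:1 in blocks, and no household or family unit of allocation is mentioned. The treated arm starts within 1 week. Controls are assessed at 12 weeks (T1a) and 20 weeks (T1b) and are treated only after the wait: "For participants in the waiting list control group, at the end of the 20-week waiting period after which they will receive online CBT". The same section presents the waitlist as giving a comparison of treatment with no treatment, relative to natural recovery.

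**The concern.** Support figures and trial participants come from overlapping circles. Two people bereaved by the same death may both enrol and be allocated to different arms, and the treated one may choose the waiting one as support figure. Treatment runs for 12 weeks from about the time of allocation, so the waiting person could be informed about the treatment, and help someone through it, before T1a and T1b.

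A control in that position is no longer clearly an untreated comparator. If the role brings any benefit, the contrast for hypothesis 1 shrinks and power falls.

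Two features of the plan might seem to cover this but do not:

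- The household level in the model accounts for correlated outcomes. It does not remove an effect that has passed from one arm to the other, and it does not include relatives or friends who live apart.
- The co-intervention question under Other measures asks only about professional help from a psychologist, therapist or psychiatrist. A control who had been a support figure would correctly answer no.

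**Working it through.** **1. The plan's own figure.** All inputs are from the Sample size section: "at least a medium effect size (f=0.25; based on prior research"), "a strong association (r=0.50) between the preassessment and postassessment", "an α of 0.017 (corrected for multiple testing, that is, 0.05/3"), 80% power, and 23 per condition (N = 46) before dropout.

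For the time-by-condition interaction in a repeated measures analysis of variance with m = 2 occasions and 2 groups:

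- λ = f² × N × m / (1 − r) = 0.0625 × 46 × 2 / 0.5 = 11.5
- degrees of freedom 1 and N − 2 = 44
- power = 81.2% at α = 0.05/3 (81.4% at α = 0.017)

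The smallest even N that reaches 80% is 46, so the stated 23 per condition reproduces.

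**2. What the effect means.** With r = 0.50 the SD of the change score is √(2 × (1 − 0.50)) = 1 baseline SD. Since λ = d² × N / 4, we have 11.5 = d² × 11.5, so d = 1.0. The planned effect is a 1.0 SD difference in change between the arms.

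**3. Dilution.** Suppose a share c of controls act as support figures and each gains a fraction b of the treatment effect. The contrast is multiplied by (1 − cb), so λ = 11.5 × (1 − cb)². The article gives neither c nor b, so both are assumptions. With N = 46 and α = 0.05/3:

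| c | b | cb | λ | Power |
|---|---|---|---|---|
| 0 | – | 0 | 11.50 | 81.2% |
| 3.75% | 25% | 0.009 | 11.29 | 80.4% |
| 10% | 25% | 0.025 | 10.93 | 78.9% |
| 10% | 50% | 0.05 | 10.38 | 76.5% |
| 20% | 50% | 0.10 | 9.32 | 71.2% |
| 30% | 50% | 0.15 | 8.31 | 65.3% |

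With 23 controls analysed, c = 10% is two or three people (23 × 0.10 = 2.3).

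**4. Which rows are plausible.** The 3.75% row assumes that 30% of controls have a co-enrolled relative, half of these pairs are split between the arms, half of the treated relatives name anyone, and half of those name the control: 0.30 × 0.5 × 0.5 × 0.5 = 0.0375.

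The lower rows ask for much more. A b of 50% means that being a support figure and reading about the treatment yields 0.5 SD of improvement. If pairs are allocated independently, so that about half are split, c = 30% needs about 60% of controls to have a co-enrolled relative (0.30 / 0.5), with every treated relative choosing that control. Nothing in the article supports inputs of that size.

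**The case against.** The strongest objection is that little flows along this path, and seldom.

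- **Content.** The active components are the lessons, the exposure and writing assignments, the cognitive and activation exercises, and the therapist's feedback. None is said to reach the support figure. A reader might infer that controls would be receiving therapy material, but the article says only that the support figure is informed about the treatment. Under Participants, candidates recruited through the survey are already sent a letter about the intervention, and a public website describes the treatment. The article does not show that the support-figure text adds anything therapeutic. This stands, although helping someone through the programme is more than reading about it.
- **Frequency.** The support figure may be any relative or friend of the participant, bereaved by the same death or not. Exposure of a control needs that person to be co-bereaved, above a symptom threshold, enrolled, allocated to the waitlist, waiting while the other is treated, and chosen. This stands too: the article calls household co-enrolment possible, not common.
- **Source.** A rule on who may be a support figure could be in the full protocol or the participant materials, which are not shown. If so, pointing to it answers the first part of the fix.
- **Detection.** The article does not say what the online framework records about support figures, so it cannot be asserted that exposed controls would be untraceable. What can be said is that the described co-intervention question would not find them.

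These arguments limit the size of the problem but do not close the path. The text as it stands permits it, and neither the household level nor the co-intervention question deals with it.

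**Conclusion.** This is a minor point that is cheap to close. On the article's text, a waitlist control can be a support figure before T1a and T1b. The exposure is probably uncommon and weak, and its size cannot be derived from the document. Any bias runs towards no difference, so the risk is an understated or missed effect, not a false positive one.

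Under the assumption of 10% of controls gaining 25% of the effect, power falls from about 81% to 79%; with rarer exposure the loss is under one percentage point. A reader might infer from the lower rows of the table that power could drop to about 65%, but that needs shares and benefits for which the article gives no basis. The point matters mainly because the planned power has little reserve above 80% and because exposure that is not recorded at the time may be hard to recover later.

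**What to change.** 1. In the Intervention section and the participant instructions, ask treated participants to choose a support figure who is not currently on the trial's waiting list.
2. Do not send support-figure information to a waitlist participant until that person's T1b questionnaire has been returned.
3. Add one yes/no item for controls at T1a and T1b: whether they acted as a support figure for a trial participant.
4. Keep the intention-to-treat analysis of hypothesis 1 as primary and report the number of exposed controls. An analysis without exposed controls may be shown as supportive only, because it removes people from one arm on the basis of something that happened after randomisation.

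The cost is an instruction sentence, a check before the information is sent, and one questionnaire item. The downside is that a few participants have a narrower choice of support figure. The article states that recruitment had not begun when it was submitted, so at that time the change could have covered every participant.
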